### Patient adherence and study discontinuation

To improve adherence to the intervention protocol, all medication or placebo injections will be administered by the research assistant at the clinical study centre, which requires the attendance of patients. Similarly, all questionnaire data will be assessed prior to the medication administration on site.

Given the relatively low dosages of secukinumab in the reinforcement groups, topical treatments will be permitted as concomitant care in all three groups to enhance adherence and reflect real-life clinical care, as recommended by the S3 guideline for the treatment of psoriasis vulgaris. The study participation will be discontinued at any time at the patient’s request, if side effects are deemed intolerable by the patient and/or the treating physician or if the patient misses more than one visit. In such cases, the patient will be unblinded to the treatment allocation to allow appropriate subsequent medical care.

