### Sample size, group allocation and blinding

#### Sample size

To test the non-inferiority of the drug-dose reduction strategy to the standard care at an exploratory level, the sample size calculation was conducted in R using the epiR package (function: epi.ssninfb). This calculation is based on a non-inferiority framework using the absolute risk difference scale. For the purpose of calculation, a favourable outcome was assumed for 70% of participants in the reinforcement group and 75% in the TAU group. The non-inferiority margin was set to an absolute risk difference of 0.25, corresponding to a minimal clinically important difference (MCID) of >25%. Assuming a one-sided α=0.05 and 80% power, a total sample size of N=152 was required for a 1:1 comparison between TAU and the pooled reinforcement groups. As the primary non-inferiority hypothesis compares TAU with the pooled reinforcement groups, the sample size calculation was based on a 1:1 allocation ratio.

To account for the dropout rate of 10% during a previous study, which investigated the impact of verbal inductions of positive treatment-related expectations as a dose-reduction strategy in patients with psoriasis,^33^ a sample size of N=168 is set.

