### Missing data handling

All primary analyses will follow the intention-to-treat (ITT) principle, including all patients who received at least one active dose of the study medication and completed the acquisition phase (ie, attended visits 0–2). Patients meeting this criterion will be included in the analysis with all available data up to the point of dropout. By contrast, individuals who only attended the baseline assessment (visit 0) will be excluded from longitudinal modelling due to the absence of any post-baseline intervention exposure (ie, no medication or conditioned stimulus was administered). Missing data will be addressed using Full Information Maximum Likelihood (FIML) as the primary estimation approach. FIML leverages all available data points, including partially observed cases, by estimating model parameters based on the observed-data likelihood, without imputing missing values. This method is particularly suitable for complex mixed-effects models and preserves statistical power while minimising bias under the assumption of data missing at random (MAR).

Given the structured nature of data collection, where all assessments are completed on-site prior to medication administration, only a low proportion of missing data is expected. Reasons for missed visits (eg, illness, psychological burden) will be documented systematically through physician–patient contact and follow-up communication. In addition, a wide range of psychometric, demographic and clinical variables (eg, depression, anxiety, acute stress, treatment satisfaction) is collected, which increases the possibility that missingness is conditionally random (ie, MAR) and can be accounted for by observed data.

To empirically evaluate the MAR assumption, we will conduct logistic regression analyses to identify variables that significantly predict the occurrence of missing data. If no such variables are found, the originally specified analysis model will be estimated using FIML, without the inclusion of auxiliary covariates, thereby ensuring consistency with the pre-specified hypothesis structure.

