However, if significant predictors of missingness are identified, multiple imputation (MI) will be employed as a complementary strategy. In this case, auxiliary variables will be included in the imputation model only, while the analysis model will remain unchanged. This allows for the modelling of potential MAR mechanisms without introducing auxiliary covariates into the hypothesis-driven analysis, thereby preserving the interpretability of the predefined main and interaction effects.

To ensure sufficient information for reliable imputation, only participants with at least 7 out of 10 observed time points (ie, ≤30% missingness) will be included in the MI procedure. Participants with fewer than 7 observed time points will not be imputed but will remain in the FIML-based analyses in line with the ITT principle. In these cases, parameters will be estimated solely based on the likelihood of the available observations, without extrapolation.

A comparison between estimates obtained via FIML and MI will serve as a sensitivity analysis, evaluating the robustness of results under different plausible missing data assumptions, while maintaining a clear separation between hypothesis testing and missing data handling.

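### The only missing-data sensitivity analysis sets one MAR method against another, on different patients, so it cannot show whether non-inferiority survives informative dropout

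*Protocol article*

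**What the plan says.** All of this is in the protocol article, under Missing data handling unless noted.

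- **Primary set.** It is called intention-to-treat and is defined as "including all patients who received at least one active dose of the study medication and completed the acquisition phase", which the article equates with attendance at visits 0 to 2. The reason given for exclusion is that patients who attended visit 0 only had no exposure to drug or beverage.
- **Primary method.** FIML on all data up to dropout, stated to rest on MAR.
- **Check of the assumption.** "To empirically evaluate the MAR assumption, we will conduct logistic regression analyses" on observed variables. If no predictor is found, FIML alone is reported.
- **Second method.** MI, only if a predictor is significant, with auxiliary variables in the imputation model. The article itself describes this as modelling MAR mechanisms. It covers "only participants with at least 7 out of 10 observed time points"; patients below that count are not imputed but stay in FIML.
- **Sensitivity analysis.** FIML against MI, described as "evaluating the robustness of results under different plausible missing data assumptions".
- **Discontinuation** (Patient adherence and study discontinuation). Participation ends, among other reasons, "if the patient misses more than one visit".

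Hypothesis 1 in the Analysis plan is non-inferiority of the pooled reduced-dose arms, judged by a one-sided 95% bound against 25%.

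**The concern.** In a non-inferiority trial of reduced dosing, the dropout that matters is a patient in a reinforcement arm who leaves because of a deterioration that the recorded scores did not yet predict. A MAR method gives that patient the course of similar patients who stayed. This pulls the arms together and favours non-inferiority. A sensitivity analysis should test that case, and this one does not, although it is described as if it did.

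Two design choices weaken it further. It is conditional on a significance screen, so it may not be run at all. When it is run, it uses a narrower group of patients than the analysis it is compared with. If the results agree, a reader will take that as reassurance; if they differ, a reader will take it as a missing-data effect. Neither inference is safe.

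A separate and smaller matter is that the label on the primary set promises more than its definition delivers.

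**Working it through.** **1. Assumptions side by side.** FIML: missingness may depend on the outcome values already observed. MI: the same, plus auxiliary variables. These are two versions of MAR. Neither lets missingness depend on the unseen value (missing not at random, MNAR). Regressing a missingness indicator on observed variables can show that data are not missing completely at random. It contains no information about the unseen values, so it cannot separate MAR from MNAR.

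**2. What the 7-of-10 rule selects.** The article's own figure is consistent: 3 of 10 missing is 30%. From Study schedule and Dosing schedule and administration, visits 1 to 8 fall at weeks 0, 1, 2, 3, 4, 8, 12 and 16; visit 9 is week 20. A second missed visit ends participation, so a patient still in the trial has missed at most one.

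| Last visit seen | Week | Observations, none / one missed | In MI? |
|---|---|---|---|
| 5 | 4 | 6 / 5 | no / no |
| 6 | 8 | 7 / 6 | yes / no |
| 7 | 12 | 8 / 7 | yes / yes |

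So MI loses everyone last seen at week 4 or earlier, and those last seen at week 8 who had missed a visit. FIML keeps them all if they attended visits 0 to 2. Itch is measured only at visits 1 to 9, so a patient last seen at visit 6 has at most 6 itch values (6/9 = 67% observed, 33% missing). The article does not say whether the count is of visits or of values of the outcome.

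**3. Can the restriction alone create a difference?** This is a simulation with assumed parameters: one arm, 40,000 patients, 10 visits, between-patient and residual SD both 12, dropout possible from visit 3, higher scores worse. A maximum likelihood fit to patients with at least 7 visits stands in for MI, without auxiliary variables. Means at visit 8:

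| Dropout mechanism | Dropout | Truth | FIML | At least 7 visits | Gap |
|---|---|---|---|---|---|
| MAR | 13% | 15.86 | 15.85 | 14.88 | 0.97 |
| MNAR | 14% | 15.83 | 15.33 | 14.60 | 0.73 |

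Under MAR, where FIML is right, the gap is 15.85 − 14.88 = 0.97. Under MNAR, where both are too favourable, it is 15.33 − 14.60 = 0.73. The gap does not tell the two situations apart. The effect on the difference between arms would depend on how dropout differs by arm.

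**4. The primary set.** The acquisition phase is weeks 0 and 1, that is visits 1 and 2. A patient dosed at visit 1 who does not attend visit 2 has been exposed, so the stated reason for exclusion does not apply, yet the patient is excluded. A patient who misses only visit 2 has missed one visit, so the discontinuation rule keeps that patient in the trial while the analysis rule removes the patient from the primary set.

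**5. How much could informative dropout matter?** The documents do not give the inputs, so this is an illustration on the planning scale. Inputs from Sample size: "a favourable outcome was assumed for 70% of participants in the reinforcement group and 75% in the TAU group"; a margin of 0.25 on the risk-difference scale; one-sided α = 0.05. The plan's own figure ("Assuming a one-sided α=0.05 and 80% power, a total sample size of N=152 was required") does not reproduce: (1.645 + 0.842)² × (0.75×0.25 + 0.70×0.30) / (0.25 − 0.05)² = 61.4, so 62 per side or 124 in total. That is a separate matter; the planned 84 per side is used here. Assumptions: reinforcement dropouts (share d) all count as failures, and TAU dropouts are MAR.

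p = 0.70(1 − d); upper bound = (0.75 − p) + 1.645 × √{[p(1 − p) + 0.75×0.25]/84}

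| d | Difference | Upper bound |
|---|---|---|
| 0 | 0.050 | 0.163 |
| 5% | 0.085 | 0.200 |
| 10% | 0.120 | 0.236 |
| 12% | 0.134 | 0.251 |
| 20% | 0.190 | 0.308 |

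The bound reaches 0.25 at d of about 11.9%.

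**The case against.** Much of the defence stands.

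- **FIML uses each patient's recorded history.** PASI and DLQI are taken at every visit and itch at visits 1 to 9. Dropout driven by failure already visible in those scores is MAR and handled correctly. Only deterioration beyond what they predict causes bias.
- **MI does condition on more than FIML.** The two are not identical assumptions. But the added variables do not admit dropout that depends on unseen outcomes.
- **The plan is not blind to efficacy-related dropout.** Reasons for missed visits are to be documented and missingness is to be modelled. Both can flag it. Neither shows what it does to the non-inferiority conclusion.
- **A tipping-point analysis may sit in an unseen analysis plan.** Its absence from an article is not itself a fault. The fault is in what the article does state: the robustness claim, the supposed test of MAR, the trigger and the threshold.

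A reader might infer more than the documents support in four places:

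- *That early leavers are removed twice.* The two groups differ. Patients with 3 to 6 observations who attended visits 0 to 2 stay in the primary FIML analysis; the threshold touches only the MI.
- *That the exclusion before visit 2 hides failures of the reduced dose.* All arms receive 300 mg in weeks 0 and 1, so the reduced dose cannot be the cause. The beverage and video already differ by arm at visit 1, but no direction of bias follows from that.
- *That the logistic regressions will usually find nothing.* About 17 dropouts are expected (10% of 168), which is few, but many variables are screened. With 20 independent null candidates (assumed), the chance of at least one p < 0.05 is 1 − 0.95^20 = 64%. Whether MI is run is simply unpredictable.
- *That the bias has a known size in points.* Any such figure needs a shortfall from the MAR prediction, and the documents give none.

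**Conclusion.** The point holds in this form. The only sensitivity analysis described compares two MAR analyses, may not be run, and when run uses different patients, so neither agreement nor disagreement bears on informative dropout. The claims that it covers different assumptions and that MAR is tested empirically are wrong as stated. The 7-of-10 rule does not fit itch. The intention-to-treat label does not match the set, whose exclusion reason leaves some dosed patients unexplained and which conflicts with the discontinuation rule; this is the weaker source of bias.

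If reduced-dose patients leave because of deterioration not foreshadowed in their scores, the error favours non-inferiority. Its size cannot be derived from the documents. The 11.9% tipping figure is an extreme, one-sided scenario on a binary scale, whereas Hypothesis 1 is tested on mixed-model estimates. It shows only that the conclusion could turn at a dropout rate near the planned 10%, which is reason enough to want the analysis. The simulation likewise rests on assumed parameters, and on the natural reading that patients below 7 observations are absent from the MI analysis.

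**What to change.** In Missing data handling:

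1. Define the primary set as all randomised patients with at least one assessment of the outcome in question, and keep the present set as a sensitivity analysis labelled modified ITT. This also removes the conflict with the discontinuation rule.
2. Say that the logistic regressions describe predictors of missingness, and drop the claim that they evaluate MAR.
3. Delete the 7-of-10 rule and the significance trigger, so that MI is always run and uses the same patients as FIML.
4. Describe FIML and MI as two MAR analyses.
5. Add a delta-adjusted MI that progressively worsens imputed values in the reinforcement arms, and report the delta at which non-inferiority is lost for each Hypothesis 1 outcome.

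Cost: revised wording, some extra programming, and possibly a less favourable robustness statement. No new data are needed, and the changes should be fixed before the data are analysed.
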